### Allocation of participants

3.9

District nursing teams from participating organizations could voluntarily sign up for the study. Allocation to the intervention or control group was determined by the participating organizations, based on pragmatic factors such as team availability, staffing, and time resources. This pragmatic approach, which includes both an intervention and a control group, allows for assessing feasibility and exploring preliminary signals of effectiveness. It aligns with Eldridge et al., who highlight the importance of early impact indicators in feasibility studies of complex interventions (Eldridge et al., 2016). This design enables and informs the refinement of the intervention and future study planning.

### Intervention group procedures

3.10

Teams assigned to the intervention group participate in the full Data Nurse intervention. Upon enrolment, team members will complete the e-learning module on person-centered shared decision-making and designated data champions will attend the train-the-trainer workshop. Teams then execute the intervention during five months, in which they will integrate the shared decision-making approach and dashboard into their routine care practice. Team leaders will register participating older adults in an online data registry, Castor, for data collection. Castor is a cloud-based platform that facilitates data collection, management, and analysis for clinical research and healthcare (CastorElectronicData Capture, 2025). Older adults in the intervention group will receive the patient preparatory tool shared decision-making prior to their initial care conversations. Throughout the intervention period, data champions will facilitate monthly team reflection sessions using dashboard insights.

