**Participants:**

A total of 14 district nursing teams, with eight intervention and six control teams, with approximately 84–109 district nursing professionals and 210–294 older adult participants will be included.

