### Participants and eligibility criteria

3.8

District nursing teams members are eligible to participate if they are actively involved in patient intake, goal-setting, and care evaluation processes. Within teams allocated to the intervention group, all team members used the shared decision-making tools and dashboard as part of usual team practice. Individual team members could, however, decide whether or not to participate in the study's data collection (e.g., questionnaires and interviews). Older adults receiving care from team members who did not take part in data collection remained eligible for inclusion, as they still received the intervention through their team. Older adults are eligible if they are aged 65 years or older and currently receive district nursing care. Older adults must have sufficient cognitive capacity to provide informed consent and participate in interviews and in-person-centered shared decision-making. In addition, older adults must be able to complete the patient preparatory shared decision-making tool in Dutch, with help from their informal caregiver, if needed (Pel-Littel et al., 2020). Older adults are excluded if they have a life expectancy of less than three months. Also, older adults with a life expectancy of <3 months or with severe physical or cognitive impairments will be excluded from the study.

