### Control group procedures

3.11

Teams assigned to the control group will provide care as usual. They will not receive the e-learning program, the patient preparatory tool shared decision-making, or training on or access to the Data Nurse dashboard. Team leaders will coordinate research activities and register older adults in Castor. Control teams will participate only in data collection.

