### Secondary outcomes

3.15

Secondary outcomes are the preliminary effectiveness of the Data Nurse intervention, assessed in both intervention and control groups.

Self-reported independent functioning will be measured using the selected domains of the TOPICS-SF that assess independent functioning (Santoso et al., 2018), a patient-reported outcome measure assessing health and functioning across multiple domains, including physical health, mental health, social support, and overall wellbeing. In the intervention group, this is measured through the patient preparatory tool shared decision-making, which incorporates the TOPICS-SF items. In the control group, older adults will complete the selected domains of the TOPICS-SF separately. As the instrument is administered through different channels, group comparability will be considered in the analysis.

Patient-reported shared decision-making reflects the level of shared decision-making in the clinical encounter from the older adults' perspective. This will be measured using the CollaboRATE questionnaire (Elwyn et al., 2013), a three-item instrument, scored from 0 to 9, that evaluates the extent to which older adults perceive their concerns to be heard and integrated into care decision-making.

District nursing care delivery patterns will be extracted from electronic nursing record data for both groups, including visit frequency, care delivery mode (in-person, phone, video), use of healthcare technology, and total care hours. Additionally, three data-informed indicators are extracted from the electronic nursing record system to explore the extent to which care activities are aligned with promoting patient independence: (1) the proportion of nursing interventions aimed at promoting independent functioning, as documented in the care plans; (2) the proportion of older adults showing improvement in care need scores between intake assessment and evaluation, or between successive evaluations; and (3) the proportion of older adults who achieved their individually set target scores per care need during the study period.

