### Recruitment and participation

3.18

Recruitment will follow a multi-level approach. District nursing care organizations affiliated with the Data Nurse project will be invited to participate. Within these organizations, contact persons will distribute invitations to district nursing teams through internal communication channels such as newsletters, online bulletin boards and team meetings. Interested teams will be contacted by the research team, who will provide detailed information about the study and participation requirements. Individual team members within participating teams will decide voluntarily whether to participate in the research activities.

Older adults will be recruited by team members from participating teams, who will identify eligible older adults from their caseload and provide them with study information and an information letter. The recruitment procedure is visualized in Fig. 3.

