##### Older adults

3.18.1.2

At baseline, characteristics of older adults who participate will be collected. These include year of birth, gender, marital status, living situation, highest level of education completed, country of birth, reason for receiving care, frequency of contact with district nursing, financial concerns, and care or support from the municipality. Additional qualitative information will be collected on older adults' living situation and municipal support.

Older adults in the intervention group will complete the patient-shared decision-making preparatory tool, based on the TOPICS-SF and covering self-reported independent functioning, general health, pain, emotional well-being, social activities, quality of life, and personal goals and wishes. In addition, they will complete the TFA questionnaire on acceptability of the patient preparatory tool shared decision-making and the CollaboRATE questionnaire on patient-reported involvement in shared decision-making. Individual interviews will be conducted to explore their experiences with person-centered shared decision-making.

Older adults in the control group will complete selected domains of the TOPICS-SF, specifically the self-reliance domain (10 items) and the social activities domain (1 item, to measure self-reported independent functioning, as well as the CollaboRATE questionnaire.

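### The tool-timing sentence does not fit the enrolment rule, and neither the listed baseline items nor improvement indicator (2) would show whether the groups differ in time since start of care

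*Protocol article*

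**What the plan says.** All references are to the protocol article.

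- **Timing of the tool (3.10, intervention group):** "Older adults in the intervention group will receive the patient preparatory tool shared decision-making prior to their initial care conversations". Section 3.15 adds that this group's TOPICS-SF items are collected through the tool, so the baseline score follows the tool's timing.
- **Eligibility (3.8), stated once for both groups:** "Older adults are eligible if they are aged 65 years or older and currently receive district nursing care". There is no limit on how long the person has been in care.
- **Recruitment (3.18), both groups:** team members approach people, "who will identify eligible older adults from their caseload and provide them with study information and an information letter".
- **Control procedures (3.11):** "Team leaders will coordinate research activities and register older adults in Castor", and "Control teams will participate only in data collection". No point in the care course is named.
- **Sample size (3.17):** the full average caseload of 30 older adults is counted as eligible in every team, intervention and control alike.
- **Baseline items for older adults (3.18.1.2):** the list includes "reason for receiving care, frequency of contact with district nursing, financial concerns, and care or support from the municipality". It contains neither a start-of-care date nor time in care.
- **Indicator (2) (3.15):** the proportion whose care need scores improve "between intake assessment and evaluation, or between successive evaluations".
- **Use of the results (4.2):** change from baseline is described, with effect sizes and confidence intervals meant to inform a later effectiveness trial.

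**The concern.** The timing sentence exists for one group only. A team that takes it at face value could reasonably favour newly referred clients, because elsewhere the article separates intake from later evaluation conversations. Control teams get no such cue. The organizations decided which teams went into which group (3.9), so nothing in the design balances time in care.

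Time since start of care could plausibly be related to change in functioning, care hours and visit frequency. It bears most directly on indicator (2), which puts change from intake and change between later evaluations into one proportion. If the two groups hold different shares of new and established clients, that proportion can differ between them with no intervention effect, and the listed baseline table would not alert the reader.

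At stake are the exploratory effect sizes carried into the design of the next trial. No formal test is affected, because section 3.13 plans none for effectiveness.

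**Working it through.** **1. Reproduce the plan's own figures.** The Abstract gives "A total of 14 district nursing teams, with eight intervention and six control teams". With 30 older adults per team and 50–70% participation (3.17):

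- Eligible: 14 × 30 = 420.
- Expected: 420 × 0.50 = 210 and 420 × 0.70 = 294. Both match the Abstract.
- Intervention: 8 × 30 = 240 eligible; 120 to 168 expected.
- Control: 6 × 30 = 180 eligible; 90 to 126 expected.

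**2. Test the literal reading of 3.10 against those figures.** The Study status section sets patient inclusion from 15 June to the end of September 2025, which is 108 days, or 108 / 30.44 ≈ 3.55 months. If only people starting care could enter the intervention group, the same participation rates would need 240 new intakes in that window:

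- 240 / 8 = 30 per team, equal to the whole average caseload.
- 30 / 3.55 ≈ 8.5 new intakes per team per month.

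The sample size therefore presumes that people already in care also enter the intervention group. Section 3.10 taken literally does not fit 3.8, 3.17 and 3.18.

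**3. Effect of a difference in mix on indicator (2), with no intervention effect.** Let a and b be the shares of new clients in the intervention and control groups. Let r and s be the improvement rates in new and established clients, the same in both groups. Then

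spurious difference = [a·r + (1 − a)·s] − [b·r + (1 − b)·s] = (a − b) × (r − s).

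The documents give none of a, b, r or s. Everything below is assumed.

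| a | b | r | s | Intervention | Control | Difference |
|---|---|---|---|---|---|---|
| 60% | 20% | 50% | 20% | 0.6×0.5 + 0.4×0.2 = 38% | 0.2×0.5 + 0.8×0.2 = 26% | +12 points |
| 60% | 20% | 20% | 50% | 0.6×0.2 + 0.4×0.5 = 32% | 0.2×0.2 + 0.8×0.5 = 44% | −12 points |
| 25% | 25% | any | any | equal | equal | 0 |

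Range of absolute size: mix differences of 0 to 60 points and rate differences of 10 to 40 points give 0 × 0.10 = 0 up to 0.60 × 0.40 = 0.24, that is 0 to 24 points.

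**4. Scale.** At an assumed 30% improving, ignoring clustering, the 95% half-width is 1.96 × √[0.3 × 0.7 × (1/n₁ + 1/n₂)]:

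- 120 versus 90: 12.5 points.
- 168 versus 126: 10.6 points.

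A 12-point artefact would be about as large as the sampling error.

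**The case against.** A reader might infer that the tool rule places the intervention group at the start of care while controls can be anyone, so that early recovery will pass for an intervention effect. The documents do not support that:

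- Section 3.10 says when the tool is handed over, not who may enrol. Eligibility and recruitment source are common to both groups, and the sample size counts both alike.
- The literal reading would require a full caseload turnover per team in about three and a half months.
- Controls are not open to registration at any time. The Study status section gives one recruitment window without distinguishing the groups.
- Table 1 schedules tool use and baseline collection in the same study month, and the timing phrase could mean the first conversations within the study.
- No figure supports early recovery in new clients. People aged 65 or older who are entering care may also be deteriorating, which would reverse the sign.

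These points stand, and they remove any claim that the groups do differ or that the bias favours the intervention.

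Two further objections carry part of their weight. The article condenses a fuller protocol, so an unlisted baseline item may still be collected, and stratification detail can belong in an analysis plan. The outcomes are also exploratory, and section 5.1 admits selection bias in general terms. Neither answers the mismatch between 3.10 and 3.8, 3.17 and 3.18, nor the pooling in indicator (2), since both are written into the stated text. Section 5.1 does not mention time in care.

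**Conclusion.** The point holds as an inconsistency with a possible consequence. The timing sentence in 3.10 does not fit the enrolment rules and sample size. The groups may differ in time since start of care, but this is not shown. If they do differ, the listed baseline items would not reveal it, and indicator (2) as defined would mix it into the between-group comparison.

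Under the assumed inputs the artefact is 0 to 24 points in either direction, and exactly zero if both groups have the same mix. That range rests wholly on assumed shares and rates. It shows how sensitive the indicator is and does not predict what will happen. The pooling in indicator (2) deserves correction whichever way 3.10 was meant.

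**What to change.** 1. Reconcile 3.10 with 3.8, 3.17 and 3.18. State whether people are enrolled at the start of care, from the whole caseload, or both, and apply the same anchor in both groups.
2. Take the start-of-care date from the nursing record, which already holds the intake assessments that indicator (2) uses, and show time in care at enrolment by group in the baseline table.
3. Report the two parts of indicator (2) separately by group: intake to evaluation, and between successive evaluations.
4. Show the other secondary outcomes for new and established clients, with one cut fixed before analysis, as supportive description.

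The cost is one date field from a source already being extracted, one baseline row and one additional table. The downside is smaller cells and wider intervals, and a stratum that is nearly empty in one group may give no contrast. With 14 teams in total, the stratified figures should be read as description only.

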### Control group procedures

3.11

Teams assigned to the control group will provide care as usual. They will not receive the e-learning program, the patient preparatory tool shared decision-making, or training on or access to the Data Nurse dashboard. Team leaders will coordinate research activities and register older adults in Castor. Control teams will participate only in data collection.

### Ethical approval and informed consent

3.12

Ethical approval for this study was granted by the Medical Ethics Committee of Amsterdam UMC [2024.0956]. All research procedures involving human participants will be conducted in accordance with institutional guidelines and the principles of the Declaration of Helsinki (World Medical Association, 2013). Written informed consent will be obtained from all participants prior to data collection. Participation is entirely voluntary, and individuals may withdraw from the study at any time without consequences for their care or professional role. Data collection up to the point of withdrawal will be retained unless the participant explicitly requests its removal. Prior to providing consent, all potential participants will receive written study information in plain language. For district nursing team members, this includes an information letter describing the study purpose, procedures, time investment, and data use. For older adults, study information will be provided in plain language, with the opportunity to ask questions and, where needed, to involve an informal caregiver in the decision to participate.

### Outcomes

3.13

Outcomes will be examined at the district nursing team, team member, and older adult levels for both intervention and control groups. All effectiveness outcomes are exploratory and intended to inform a future randomized controlled trial: no formal hypothesis testing will be conducted on effectiveness measures.

### Primary outcomes

3.14

Primary outcomes concern feasibility, acceptability, fidelity, barriers and facilitators, and experiences related to the Data Nurse intervention. These outcomes will be assessed using a mixed-methods approach combining quantitative instruments and qualitative data collection.

**Feasibility** refers to the extent to which the intervention can be successfully used or carried out by the intended users in routine district nursing practice. Feasibility will be measured in district nursing team members and older adults from the intervention group using the Feasibility of Intervention Measure (FIM), a five-item Likert scale assessing perceived implement ability (Weiner et al., 2017). The feasibility of the two components of the total intervention will be assessed in team members; the feasibility of the patient preparatory tool shared decision-making will be assessed in older adults.

**Acceptability** concerns the degree to which nursing professionals and older adults consider the intervention appropriate, relevant, and worthwhile (Sekhon et al., 2017). Acceptability will be measured in nursing professionals and older adults from the intervention group using a questionnaire based on the Theoretical Framework of Acceptability (TFA), assessing affective attitude, perceived burden, ethicality, coherence, perceived effectiveness, self-efficacy, and opportunity costs on a 5-point Likert scale (Sekhon et al., 2017). The acceptability of the total intervention will be assessed in nursing professionals; the acceptability of the patient preparatory tool shared decision-making will be assessed in older adults.

**Fidelity** addresses whether the intervention is delivered as intended, including completion of training, use of the shared decision-making approach and patient preparatory tool shared decision-making, and dashboard engagement. Fidelity will be measured in nursing professionals from the intervention group using self-developed questionnaires (Supplementary File 3), tracking adherence indicators such as e-learning completion, use of stepwise person-centered shared decision-making from the e-learning, patient preparatory tool shared decision-making usage, and dashboard interactions. Teams complete these questionnaires on Castor one week before monthly online fidelity meetings with researchers, data champions, and team leaders. During these meetings, participation and delivery will be discussed using the Kotter framework (Kotter, 1996). Team logbooks will be used to document participation and implementation challenges throughout the intervention period, complementing the structured meeting discussions. Fidelity is considered high when ≥80% of teams completed the planned activities, consistent with commonly used thresholds for high intervention fidelity in implementation research (Borrelli, 2011).

**Barriers and facilitators** are factors that hinder or support the implementation of an intervention, encompassing motivation, capability, organizational readiness, and context (Huijg et al., 2014). Barriers and facilitators will be identified among nursing professionals in the intervention group using the Theoretical Domains Framework (TDF) questionnaire, covering these domains on 5-point Likert scales (Huijg et al., 2014).

**Experiences** will be measured regarding how nursing professionals and older adults perceive and reflect on working with the intervention in daily practice, including how it fits within existing workflows, how it shapes conversations and decision-making with older adults, and what unexpected effects, learning points or adaptations emerge during use. This compliments the other primary outcomes by providing in-depth, contextualized insights that cannot be caputered through standardized scales such as FIM, TFA en TDF.

A self-developed questionnaire captures nursing professionals' experiences with using the stepwise person-centered shared decision-making method in practice (supplementary file 4.).

Qualitative data on all primary outcomes will be collected through focus groups with nursing professionals from the intervention teams and individual interviews with older adults from the intervention group, exploring perceived feasibility, acceptability, barriers and facilitators, and experiences with the intervention including the patient preparatory tool shared decision-making and the dashboard. Focus groups and interviews will be conducted halfway through the study.

### Secondary outcomes

3.15

Secondary outcomes are the preliminary effectiveness of the Data Nurse intervention, assessed in both intervention and control groups.

Self-reported independent functioning will be measured using the selected domains of the TOPICS-SF that assess independent functioning (Santoso et al., 2018), a patient-reported outcome measure assessing health and functioning across multiple domains, including physical health, mental health, social support, and overall wellbeing. In the intervention group, this is measured through the patient preparatory tool shared decision-making, which incorporates the TOPICS-SF items. In the control group, older adults will complete the selected domains of the TOPICS-SF separately. As the instrument is administered through different channels, group comparability will be considered in the analysis.

Patient-reported shared decision-making reflects the level of shared decision-making in the clinical encounter from the older adults' perspective. This will be measured using the CollaboRATE questionnaire (Elwyn et al., 2013), a three-item instrument, scored from 0 to 9, that evaluates the extent to which older adults perceive their concerns to be heard and integrated into care decision-making.

District nursing care delivery patterns will be extracted from electronic nursing record data for both groups, including visit frequency, care delivery mode (in-person, phone, video), use of healthcare technology, and total care hours. Additionally, three data-informed indicators are extracted from the electronic nursing record system to explore the extent to which care activities are aligned with promoting patient independence: (1) the proportion of nursing interventions aimed at promoting independent functioning, as documented in the care plans; (2) the proportion of older adults showing improvement in care need scores between intake assessment and evaluation, or between successive evaluations; and (3) the proportion of older adults who achieved their individually set target scores per care need during the study period.

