**Intervention preparation**										
	Use patient preparatory tool shared decision-making	Older adults (I)			**X**					
	shared decision-making e-learning	DNT members (I)			**X**					
	Follow dashboard workshop	Data champions + older adults (I)			**X**					

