### Limitations and challenges

5.1

Several limitations should be acknowledged. The non-randomized design may introduce selection bias, though this reflects the operational constraints of district nursing practice and is consistent with recommendations for feasibility studies (Eldridge et al., 2016). Self-reported fidelity measures may be subject to social desirability bias, which will be mitigated through triangulation with team logbooks and structured monthly meetings. The five-month intervention period may be insufficient to capture the full adoption of a complex behavioral intervention. The comparability of the selected domains of the TOPICS-SF data between groups warrants attention, as the instrument is administered through different channels. Finally, the limited number of clusters may constrain the statistical analysis of secondary outcomes. The findings will inform whether the intervention warrants a larger effectiveness trial, which components require refinement, and what implementation strategies are needed across district nursing contexts.

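### TOPICS-SF functioning is collected inside the intervention's own tool in one group and on a separate form in the other, so channel is aliased with group at each time point and change scores remove it only under an untestable condition

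*Protocol article*

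**What the plan says.** **Channel.** Protocol article, section 3.15, on the intervention group: "In the intervention group, this is measured through the patient preparatory tool shared decision-making, which incorporates the TOPICS-SF items". On controls: "In the control group, older adults will complete the selected domains of the TOPICS-SF separately". Section 3.11 confirms that controls never see the tool: "They will not receive the e-learning program, the patient preparatory tool shared decision-making".

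**Content.** Section 3.18.1.2 describes the tool as "covering self-reported independent functioning, general health, pain, emotional well-being, social activities, quality of life, and personal goals and wishes". The control form holds selected domains, "specifically the self-reliance domain (10 items) and the social activities domain (1 item"), so 11 items in all. Section 3.5 makes the tool the basis of the nurse's shared decision-making conversation.

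**Timing.** Table 1 marks the modified TOPICS-SF for both groups at baseline (June) and close-out (November). The row "Use patient preparatory tool shared decision-making" is marked in June only, under intervention preparation.

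**Analysis.** Section 4.2 plans a descriptive look at change from baseline to follow-up in the secondary outcomes, with effect sizes and confidence intervals intended for the design of a later effectiveness trial. Section 3.13 calls all effectiveness outcomes exploratory and rules out formal testing.

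**Acknowledgement.** Section 3.15 says "As the instrument is administered through different channels, group comparability will be considered in the analysis", and section 5.1 says "The comparability of the selected domains of the TOPICS-SF data between groups warrants attention, as the instrument is administered through different channels". Neither names a method.

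**The concern.** One group reports functioning in a document that invites reflection on goals and then feeds a care conversation with the nurse. The other answers a short research form for which no such role is stated. Patients may rate the same ability differently in these two settings. No group of participants answers through both channels, so the data say nothing about how large that shift is.

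This is the only patient-reported measure of independent functioning, which the intervention targets and which is named in the secondary aim. A shift due to channel could be read as an effect of the intervention, or could hide one, and the resulting effect size is meant to inform a larger trial. Its confidence interval would show sampling error but not this bias.

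**Working it through.** **1. The plan's own figures.** Section 3.17 gives 14 teams with an average caseload of 30: 14 × 30 = 420 eligible older adults. At 50–70% participation this is 210–294, as in the abstract. These figures reproduce. The bias argument does not depend on them.

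**2. Model.** Let G = 1 for intervention, T = 1 for November, and C = 1 when the items are answered inside the tool. The four group-by-time means are

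mean = β0 + β1·G + β2·T + β3·G·T + m·C

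Here β3 is the difference in change that one wants, and m is the channel offset in SD units. There are four cell means and five parameters, so something must be inseparable. What that is depends on when the tool is used.

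**3. Single time point, tool in the intervention group.** C = G. The columns for intercept, group and channel have rank 2 of 3. The group difference estimates the true difference plus m. Patient covariates do not help, because C does not vary within group.

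**4. Tool at both times.** C = G at both times; rank 4 of 5. Intervention change is β2 + β3 and control change is β2, so the difference is β3. The offset cancels if it is additive and the same in June and November. If it halved by November, the difference would be β3 − m/2.

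**5. Tool in June, stand-alone form in November.** C = G·(1 − T); rank 4 of 5, and β3 is not estimable. Intervention change is (β1 + β2 + β3) − (β1 + m) = β2 + β3 − m, and control change is β2. The difference is β3 − m. The November contrast is then free of channel but equals β1 + β3. The June contrast is β1 + m, so the pre-existing group difference β1 cannot be recovered from baseline.

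**6. Size with a true effect of zero.** The documents give no value for m. The assumed range is 0.1 to 0.5 SD.

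| Assumed m (SD) | Single-time difference, tool in use | Change, tool both times, constant offset | Change, offset halves | Change, switch to stand-alone form |
|---|---|---|---|---|
| 0.1 | 0.1 | 0 | −0.05 | −0.1 |
| 0.2 | 0.2 | 0 | −0.10 | −0.2 |
| 0.3 | 0.3 | 0 | −0.15 | −0.3 |
| 0.5 | 0.5 | 0 | −0.25 | −0.5 |

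**7. Scale against sampling error (illustrative).** Assume an intracluster correlation of 0.05, which is not in the documents, and equal recruitment per team.

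- 210/14 = 15 per team gives 120 v 90. SE = √(1/120 + 1/90) = 0.139; design effect 1 + 14 × 0.05 = 1.70; half-width 2.18 × 0.139 × √1.70 = 0.40 SD.
- 294/14 = 21 per team gives 168 v 126. SE = √(1/168 + 1/126) = 0.118; design effect 1 + 20 × 0.05 = 2.00; half-width 2.18 × 0.118 × √2.00 = 0.36 SD.

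The multiplier 2.18 is t on 14 − 2 = 12 degrees of freedom. These are half-widths for an unadjusted difference at one time point, not for the planned change comparison. An offset of 0.1 to 0.3 SD is between 0.1/0.40 = 25% and 0.3/0.36 = 83% of them.

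**8. Which case applies.** Section 3.15 ties the intervention group's measurement to the tool without limiting it to baseline, and Table 1 marks the outcome in June and November. Together these imply step 4. Table 1's June-only row for the tool points to step 5. The article does not settle it.

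**The case against.** The strongest reply has four parts.

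- **Same items.** A reader might infer that the groups answer different instruments. The article does not say that: the tool incorporates the TOPICS-SF items, and Table 1 lists one instrument for both groups. Section 3.18.1 has older adults complete questionnaires on paper without distinguishing groups. The help from an informal caregiver in section 3.8 is part of an eligibility criterion for older adults generally, and nothing bars help with the control form. What differs is channel, context and length. This stands.
- **Change scores.** A reader might infer that no analysis could ever remove the problem. That is too strong, because step 4 shows a constant offset cancelling. But constancy cannot be tested here. It is also doubtful, since the November answers follow five months of the intervention.
- **November form.** A reader might take it as established that the intervention group switches to a stand-alone form. It is not: the June-only row schedules an intervention step, and section 3.15 can be read as the tool at both times. It is an ambiguity to resolve.
- **Exploratory and disclosed.** The outcome is secondary and untested, and the issue is stated twice. How comparability is considered could be left to an analysis plan that is not shown. The first part limits the severity. The second does not remove the point, because the missing information lies in the design: no later plan can estimate m when no group uses both channels.

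**Conclusion.** The point holds in limited form. As section 3.15 describes it, channel and context are completely aliased with group at each time point, and covariate adjustment cannot separate them. The planned difference in change is free of the offset only if the tool is used both times and the offset is additive and constant. If the intervention group switches form, the offset enters in full with opposite sign. The sizes in the table rest on an assumed m; the direction and the one-for-one transfer do not.

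The point concerns one exploratory secondary outcome. A reader might infer that the feasibility findings are undermined. They are not: the primary outcomes are assessed in the intervention group only, and neither CollaboRATE nor the record-based indicators are collected through the tool. It matters because an effect size from this comparison is meant to inform a future trial. It is a cheap improvement, not a condition for the study to stand.

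**What to change.** **If forms can still be set, and for any later trial:** give both groups the same stand-alone 11-item paper form at baseline, before the tool is handed out, and again in November. Base the outcome on that form only, and keep the tool purely as an intervention component. Channel then drops out of the model. The cost is eleven duplicated items for intervention patients at each time the tool is also completed, plus protocol wording.

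**Where data are already collected** (collection was planned for June to November 2025):

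- State which form the intervention group completed in November, and reconcile section 3.15 with Table 1.
- Replace the sentence about considering comparability with a plain statement that channel coincides with group and its effect cannot be estimated.
- Report the between-group TOPICS-SF effect size as not interpretable as an intervention effect, and do not use it to plan the future trial.
- If a common form was used in November, a November comparison may be shown, but only with the caveat that the organizations allocated teams without randomization (section 3.9) and the groups are not adjusted for comparably measured baseline functioning. A November-only comparison is not a general remedy: if the tool was used in November, it carries the whole offset.

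These changes cost only wording.
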